### Objectives and Hypotheses

The objective of this trial is to evaluate the efficacy of the GAD Online and Lantern programs for Indian university students with clinical or subthreshold GAD. The primary hypothesis is that the use of either of the active intervention groups, the unguided GAD Online program or the guided Lantern program, for 3 months will lead to greater GAD symptom reduction than will be seen among students in the wait-list control group. The secondary hypothesis is that a guided intervention (Lantern) will lead to greater user engagement and symptom reduction than the unguided intervention (GAD Online). In addition, it is hypothesized that the use of either program will lead to greater functional gains (eg, social functioning) and improvements in mental health self-efficacy than will be seen among students in the wait-list control condition. Table 1 provides a summary of the trial outcome measures.

## Methods

### Stakeholder Engagement

To better understand the cultural context, existing mental health care system, and needs, a community-based participatory research (CBPR) methodology was used [41]. CBPR calls for a collaborative approach to research that involves all stakeholders in the research process to ensure findings and knowledge gained are meaningful to the community and recommendations are feasible to implement and sustainable. A series of interviews and co-learning discussions were conducted with the following key stakeholders: university administration, existing on-campus counselors and medical professionals, faculty mentors, hostel wardens, and student groups. In interviews with university administration, key topics addressed included current student welfare priorities and where mental health care falls on the list, successful and failed student outreach and engagement efforts, perspectives and concerns of parents, and potential budget for implementing and sustaining new mental health care resources. On-campus counselors provided insight into the typical structure of counseling in Indian school and university environments and the relationship between administration and provider, particularly highlighting that ethics around patient/student privacy are not as widely or consistently practiced in India. Faculty provided the perspective of a “mentor” who primarily gets assigned students flagged for poor academic performance. Hostel wardens provided insight into how “trouble cases” are identified and triaged. Finally, students shared information on student knowledge of resources, barriers that exist to accessing them, and the general campus culture around mental health, particularly noting the stigma around anything involving the term “mental.” The details and results of these qualitative assessments will be written up separately.

### Preliminary Feasibility and Acceptability Evaluation

To evaluate the feasibility of disseminating these programs to university populations in India, interviews were conducted with university administration to assess the ability to conduct outreach initiatives to engage and educate students about these programs and circulate a campus-wide online survey to assess students’ mental health and connect those with significant symptoms to online interventions. Administrators were interested in the proposed survey-linked-to-intervention approach, specifically noting students’ interest in opportunities that might allow them to access help privately and on their own time; however, they expressed hesitation about whether students would actually use online programs for mental health care.

To evaluate the acceptability of these Internet-based mental health care interventions among the Indian university student population, a presentation and survey was conducted in April 2014 at one Indian university. Following a presentation to an auditorium of nearly 300 students about anxiety and online programs designed to reduce associated symptoms, students were invited to the adjacent computer laboratory to complete an online survey assessing anxiety symptom severity and student interest in using these types of online programs. The survey was completed by 78 undergraduate students (aged over 18; 52% male). Of these, 94% (73/78) indicated they would consider using “a mobile phone app-based “coached” program” to help them with anxiety symptoms (the Lantern Internet program is mobile optimized so users accessing the website via their mobile phones can have a similar experience to those able to use the iPhone iOS mobile app; therefore, the language “app based” was used). The majority (55/78, 70%) indicated they would like to be contacted should these programs become available at their college.

Of the students who completed the survey, 10% (8/78) had clinical GAD as measured by the 5th Edition of the Diagnostic and Statistical Manual of Mental Disorders (DSM-5) criterion-based scoring of the GAD-Q-IV [42], and an additional 22% (17/78) had subthreshold GAD, defined as a score of 5.7 or above on the GAD-Q-IV but not being clinical. Additionally, 24% (19/78) had clinical social anxiety as measured by DSM-V criterion-based scoring of the Social Phobia Diagnostic Questionnaire (SPDQ) [43], 13% (10/78) scored above a clinical cutoff of 8.75 on the Panic Disorder Self Report (PDSR) [44], and 8% (6/78) scored above a clinical cutoff of 38 on the PTSD Checklist for DSM-V (PCL-5) [45]. The prevalence is roughly comparable with that reported by Raakhee and Aparna [46] in a population (N=100) of higher secondary students in India: 13% GAD, 15.6% social anxiety, 15% panic disorder, with 56.8% of all students experiencing 1 or more types of anxiety disorders. Similarly, the prevalence of GAD is comparable with the 19% found by Sahoo and Khess [6] via clinical interviews in a population (N=405) of young adult males in an Indian university. This informal assessment bolstered the belief that the Indian university student population is interested in and might benefit from access to Internet-based interventions addressing anxiety.

### Setting

The trial will be conducted in 3 private colleges in Hyderabad, Telangana, a city in the south of India.

### Design

A parallel arm, 3 (condition) × 3 (time) randomized controlled trial with equal allocation of students between arms will be used. Students will be randomized to the unguided GAD Online intervention, the guided Lantern intervention, or a wait-list control group. Those assigned to the GAD Online or Lantern group will have full program access for 3 months. Outcomes will be assessed at screening/baseline, postintervention (3 months), and 6-month follow-up (9 months).

### Participants and Procedures

#### Recruitment

The flowchart (Figure 1) shows the process of recruitment and follow-up of students in the trial. Potential participants will be recruited through an online survey delivered across 3 colleges in Hyderabad. The research coordinator will visit each site and deliver presentations about the study as well as send campus-wide emails. After raising awareness about the study across the campus, the research coordinator will circulate a link to an online survey via email, which will also be posted in the student Facebook page and other social media groups. The landing page will again provide information about the study and instruct interested individuals to move forward to complete an online consent form and screening survey. This landing page will also contain the contact information of the on-campus counselor, as this information is meant to be available to all students across campus.

Those who meet criteria for clinical or subthreshold GAD will be invited to participate in the study and use an online program. Those who are interested will be informed that they will be assigned to a condition within 4 weeks. Everyone will receive their assignment email within 4 weeks following baseline, and those assigned into the 2 treatment conditions may activate their program account and begin immediately. Students in the GAD Online or Lantern conditions will have access to the intervention over a 3-month period. Students assigned to GAD Online can access content at whatever pace they choose. Students assigned to Lantern can access up to1 session per day because the program is structured to build mastery. Program access will be disconnected following this period. If students still meet clinical criteria for GAD at the end of the intervention, they will receive a referral to visit the on-campus counselor. Students will also be given a list of free, publicly available online self-help resources for anxiety (eg, Mental Health Online, ThisWayUp). Continuation in the guided intervention will not be possible due to resource constraints around program coach availability in the context of this research trial. Assessments will be conducted completely online. At each assessment time point, students will receive an email with a link to an online survey hosted on Qualtrics, an online survey platform with industry-standard data security measures.

**Figure 1 figure1:**
[figure not shown]
Trial flow chart.

#### Eligibility

Eligible participants will be current students of the colleges, all of which are English medium, aged 18 or older who provide their email address, informed consent to complete the study, and meet criteria for clinical or subthreshold GAD. This age range was chosen because individuals younger than 18 require parental consent for participation in research. Based on self-report responses in the online survey, students are categorized into clinical, subthreshold, and asymptomatic for GAD. Those who meet DSM-V diagnostic criteria for GAD as measured by criterion-based scoring of the 4th edition of the Generalized Anxiety Disorder Questionnaire (GAD-Q-IV) [42] are classified as clinical, or more realistically,

“a probable diagnosis of GAD based on self-report.” To note, the diagnostic criteria did not change from DSM-IV to DSM-V, and therefore the GAD-Q-IV questions can still be used to assess DSM-V GAD criteria. Those who score 5.7 or above using dimensional scoring of the GAD-Q-IV but are not clinical are classified as “subthreshold.” All others are asymptomatic. It is also important to note that clinical diagnosis should be established using a clinical interview, which is not feasible in this study, thus the use of the self-report measures. Moreover, this study’s aim is not to provide diagnoses to students but rather to use gold-standard instruments to provide appropriate “matches” between students and available resources (ie, the research study or referral).

The PTSD Checklist for DSM-V (PCL-5) [45] will be used to refer individuals who self-report clinical symptoms of PTSD to targeted intervention or clinical services. CBT for GAD has been demonstrated to improve symptoms across comorbid disorders such as social anxiety disorder and depression [47], and therefore a “pure GAD” sample is not necessary. However, PTSD requires a more specific approach, and data on CBT for GAD’s impact on PTSD are not available. A more conservative approach was followed: PTSD “probability” based on the PCL-5 (ie, scoring 38 or above) will result in a referral to seek help from the on-campus counselor and to access the free, publicly available iPhone and Android mobile app, PTSD Coach [48]. It is difficult to get a “clean sample,” so a balance between safety and generalizability was pursued. No additional symptom-based exclusion criteria were imposed, because a primary goal of this study was to connect most students to a service they might be willing to access. Once a student is connected to a program, mechanisms exist to ensure referrals are given if symptoms are not adequately reduced and/or other symptoms present themselves (eg, program coaches give referrals to those in the guided Lantern intervention and postintervention survey feedback gives referrals to those who still report clinical symptoms). Any individuals who report currently receiving mental health treatment will also be excluded from enrolling in the study and receiving a program. Following rule-out, individuals with a clinical or subthreshold GAD classification will be invited to participate in the study evaluating online interventions. Those who accept will be randomized to one of three conditions: a self-help program (GAD Online), a guided self-help program (Lantern), and a wait-list control group. A complete list of inclusion/exclusion criteria can be found in Textbox 1.

Inclusion and exclusion criteria for the study.Inclusion criteria18+ years oldCurrent student at the universityMeet DSM-V criteria using criterion-based scoring on the GAD-Q-V (clinical) OR score ≥ 5.7 using dimensional scoring of the GAD-Q-IV but not meet DSM-V clinical criteria (subthreshold)Provide an email addressConsent to participate in the studyExclusion criteriaCurrently receiving mental health treatmentCurrent diagnosis of PTSD (PCL-5 score ≥ 38)

#### Ethical Concerns and Consent

The trial protocol has been granted ethical approval by the Institutional Review Board at Stanford School of Medicine (protocol number 31629) and governing bodies at each of the participating colleges. The protocol is registered with ClinicalTrials.gov (NCT02410265).

In the online consent form, students are notified of how their privacy and confidentiality of their data will be maintained. All survey data will be gathered and stored on Qualtrics, an online survey platform with industry-standard data security measures. Students are informed that their participation in the survey or in a program is private and will not be shared with their college, their parents, their peers, etc. Furthermore, all data gathered will be aggregated and deidentified prior to use in any publications. Only the research coordinator has access to identifying student data. Program coaches assigned to work with students in the guided Lantern intervention connect with students via the secure program platform; no personal contact information (eg, email, phone number) is exchanged. As Lantern users receive email notifications when they receive a message from a program coach, Lantern has access to the student users’ emails; however, Lantern is HIPAA compliant and follows appropriate data management and sharing protocols. Students assigned to the GAD Online intervention are provided with generic account user names and passwords, meaning GAD Online never has need for or access to students’ email addresses.

#### Baseline Assessments

After giving online consent, students complete the baseline assessment, which also serves as the screen for eligibility. Table 1 provides a summary of the measures that will be used.

#### Randomization

Randomization will be carried out by the research coordinator after the baseline assessment. Random allocation to the treatment groups will occur within 4 weeks after the screening/baseline survey has been completed. The algorithm for random allocation will consist of a stratified block design, with stratification by level of symptoms (clinical or subthreshold) and a block size of 6. There will be 2 strata, corresponding to clinical/subthreshold symptom level. Allocation will be administered using Randomizer, a Web-based patient randomization service for clinical trials.

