**Methods:**

Students will be recruited via 3 colleges in Hyderabad, India, and referred for a campus-wide online screening. Self-report data will be collected entirely online. A total of 300 qualifying students will be randomized in a 1:1:1 ratio to receive GAD Online, Lantern, or to be in a wait-list control condition, stratified by clinical and subthreshold GAD symptomatology. Students will complete a postintervention assessment after 3 months and a follow-up assessment 6 months later, at which point students in the wait-list control condition will receive one of the programs. The primary outcome is GAD symptom severity at 3 months postintervention. Secondary outcomes include GAD caseness at 9 months, other anxiety and depression symptoms, self-efficacy, and functional measures (eg, sleep, social functioning) at 3 and 9 months, respectively. Primary analyses will be differences between each of the intervention groups and the wait-list control group, analyzed on an intention-to-treat (ITT) basis using mixed-design ANOVA.

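### A single fixed block size of 6, with the recruiting coordinator also running randomization, leaves the order of entry open to foreknowledge if students are entered one at a time

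*Protocol article*

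**What the plan says.** The protocol article, under Randomization, describes a stratified block design with "stratification by level of symptoms (clinical or subthreshold) and a block size of 6". It adds: "There will be 2 strata, corresponding to clinical/subthreshold symptom level". College is therefore not a stratum. The abstract gives the ratio and size: "A total of 300 qualifying students will be randomized in a 1:1:1 ratio to receive GAD Online, Lantern, or to be in a wait-list control". Each block of 6 thus holds two places per arm.

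The same section states: "Randomization will be carried out by the research coordinator after the baseline assessment". Allocation may fall at any point in the 4 weeks after the baseline survey. The tool is also named: "Allocation will be administered using Randomizer, a Web-based patient randomization service for clinical trials".

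The role that randomizes has two other duties:
- Under Recruitment: "The research coordinator will visit each site and deliver presentations about the study as well as send campus-wide emails".
- Under Ethical Concerns and Consent: "Only the research coordinator has access to identifying student data".

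No blinding is described. A coached program, an unguided program and a wait-list are recognisable for what they are, and under Risk Management Protocol the unguided students are told that nobody monitors them. The primary outcome is the self-reported GAD-Q-IV.

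**The concern.** A web service hides the list of future allocations. It does not hide what can be worked out from a known block size and the allocations already issued. Once five places in a block of 6 are known, the sixth is fixed, and sometimes the fifth is too.

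The person placed to make that deduction is also the person who enters the students. The article sets a window for allocation but no rule for the order of entry. Recruitment ran for 3 weeks at each college and the window is 4 weeks, so several students with baseline scores already recorded could be waiting at once. Someone who knew the next place could choose which of them took it, or hold one back.

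What is at stake is allocation concealment. If the choice followed severity within a stratum, or apparent motivation, the arms could differ at the outset. The comparison of each program with the wait-list rests on an unblinded self-report, which would not correct such a difference.

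**Working it through.** **The plan's own figure.** The article gives no figure for predictability. Its related figure, 64 per group, reproduces: an effect size of 0.5 (1.73/3.46), 80% power and two-sided 5% (sidedness assumed) give 63.77 per group by the two-sample t-test, rounded up to 64. The present point does not affect it.

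**Inputs.** Three arms at 1:1:1, a fixed block of 6 with two places per arm, and N = 300.

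**Assumptions, not stated in the article.** Students are entered one at a time; the person entering them knows the block size and all earlier allocations in the stratum; blocks are complete (300/6 = 50 blocks).

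**Method.** A block has 6!/(2!·2!·2!) = 90 equally likely orderings. One arm's two places are equally likely to be any of the 6×5/2 = 15 pairs of positions. Before each place is filled:

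| Place | Arm certain | Active vs wait-list certain | At least one arm excluded | Best guess right |
|---|---|---|---|---|
| 1 | 0 | 0 | 0 | 1/3 = 0.333 |
| 2 | 0 | 0 | 0 | 2/5 = 0.400 |
| 3 | 0 | 1/15 = 0.067 | 3/15 = 0.200 | 0.500 |
| 4 | 0 | 3/15 = 0.200 | 9/15 = 0.600 | 0.6×2/3 + 0.4×1/3 = 0.533 |
| 5 | 3/15 = 0.200 | 6/15 + 1/15 = 0.467 | 1 | 0.2×1 + 0.8×1/2 = 0.600 |
| 6 | 1 | 1 | 1 | 1 |
| Sum | 1.200 | 1.733 | 2.800 | 3.367 |
| Sum/6 | 20.0% | 28.9% | 46.7% | 56.1% |
| Of 300 | 60 | about 87 | 140 | – |

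The fifth place is certain when the last two places belong to the same arm: 3 arms × 1/15. Active versus wait-list is settled when both wait-list places are used up, or when only wait-list places remain. Under simple randomization the best guess would be right 33.3% of the time.

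**Varying block sizes.** This was simulated for an observer who knows the set of sizes but not the size of the current block, each size being equally likely. As a check, the same simulation with fixed blocks of 6 returns 20.0% and 56.1%.

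| Block sizes | Certain | Best guess right |
|---|---|---|
| 6 only | 20% | 56% |
| 6 and 9 | about 5% | 54% |
| 6, 9 and 12 | about 2.5% | 53% |

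Varying the size nearly removes certainty but hardly reduces informed guessing, so it is the weaker of the two safeguards.

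**The case against.** The strongest reply is that the percentages depend on a procedure the article does not describe. A 3-week recruitment period followed by assignment within 4 weeks fits loading students in batches as well as entering them singly. If they were loaded in one batch per stratum, prediction from earlier allocations would largely vanish. The article also does not say whether the coordinator knew the block size during allocation. This stands: the figures are an upper bound under stated conditions.

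Second, the usual route to selection bias is mostly closed. Under Eligibility and Baseline Assessments, consent, self-report screening and baseline are completed online, and students accept before they are randomized. Recruitment is by group presentation, email and a survey link, not by individual enrolment decisions. Stratification confines any reordering to one symptom level, and baseline GAD-Q-IV is a time point in the model. This also stands. It narrows the exposure to the order and timing of entry, but does not remove it.

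Third, a fixed block run through a web service is common, and an article may leave entry procedures to the full protocol. That is fair for the order of entry. The fixed size, the coordinator's role and the window are nonetheless stated, and the combination can be improved.

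A reader might go further and infer that 60 allocations were in fact predictable, that the coordinator could steer who enrolled, or that someone reordered students. The documents support none of these. The first needs single entry and known block size, the second is blocked by the sequence of consent and screening, and nothing points to the third. Nor does printing the block size show foreknowledge, because the article reports recruitment as already carried out.

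**Conclusion.** The point holds in a limited, conditional form. A fixed block of 6, entered by the person who recruits and holds identities, in a trial with recognisable arms and no stated order of entry, is weaker than it needs to be. If entry is one at a time and both the block size and earlier allocations are known, up to 20% of allocations are certain, active versus wait-list is certain for about 29%, and a best guess is right 56% of the time. That is at most one allocation in five with certainty, not most of them.

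The resulting bias in the GAD-Q-IV contrast cannot be estimated from the article. It would require someone to act on the knowledge, and could work only through the order and timing of entry within a stratum. The severity is low; the reason to act is that the remedy is cheap.

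**What to change.** 1. **Main safeguard.** For each college, enter all eligible students who have accepted as one locked list in order of survey timestamp, before any allocation on that list is revealed. This removes discretion over order, including where a part-filled block carries over from one college to the next. The existing 4-week window permits it.
2. **Supplement.** Use randomly varying block sizes, for example 6, 9 and 12, set in the randomization service and not disclosed to the coordinator.
3. **Students already randomized.** Report the order in which they were entered, whether singly or in batches, and who knew the block size at the time.

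The cost is one setting, one procedural sentence and a slightly larger chance imbalance in arm sizes. The sample size does not change. If allocation is complete, only the third item can still be applied in this trial.
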